### Outcomes

The primary outcome measure is retention in OAT. Retention in treatment will be calculated starting on the date of randomization and until the patient is discharged or the trial ends. Patients who are registered as having completed a successful course of treatment will be considered censored at the date of discharge, as was the case in the pilot trial [23]. Any reason for discharge, other than completed treatment, will be considered dropout, even if discharge is on patient request. In general, discharge occurs when the patient no longer receive any services. Note that practices may vary slightly between sites in terms of their practices when discharging patients. As researchers we are legally and practically unable to influence these decisions. None of the participating sites discontinue OAT against patients’ wishes, neither because of substance use, nor because of failure to attend treatment. Only the present episode is considered in this trial (i.e., the episode that is initiated or ongoing at the time of randomization).

The secondary outcomes are 1) substance use other than prescribed medications (AdultMAP) [1]; 2) self-reported days in the last month with offences for profit (AdultMAP); 3) substance use and everyday functioning (concentration, planning, keeping appointments, sleeping, eating habits, cleaning etc.) in the last month (AdultMap) and last week (WOM); 4) social interaction with individuals (family, friends, acquaintances) with non-criminal behavior and/or with no substance abuse in the last month (AdultMap); 5) employment/educational activities in the last month (AdultMap).

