### Eligibility criteria

Inclusion criteria are as follows: 1) seeking or currently receiving treatment for opioid use disorder at one of the participating sites; 2) over 18 years of age; 3) able to attend the evaluation and treatment sessions 4) score of three or above on the YouthMap12 Externalizing difficulties subscale [1].

Patients will be excluded if they have a severe mental disorder (e.g. current psychosis), cognitive difficulties, or severe aggressive and chaotic behavior that would preclude their participation in the counselling sessions.

Social workers and/or nurses at each participating site will assess whether an individual is eligible for study participation according to the eligibility criteria during the first in-person contact with the participating treatment sites, or among the patients already enrolled in OAT at the sites. If the individual is deemed eligible, the same employee will inform the individual about the trial verbally, and provide a participant information sheet. If the individual gives informed consent for study participation, the employee will collect the necessary information for randomization in an online questionnaire, which will be forwarded to the Centre for Alcohol and Drug Research, Aarhus University via an anonymous and secure email. The research team will ensure the confidentiality of this data by keeping the online questionnaire data and consent forms stored on secured servers. After randomization, the study participant will be assigned to one of the two treatment conditions that are tested in the study. Participants and clinicians cannot be blinded to the conditions that the participants will be randomized to, but the persons who will conduct the assessments at the follow-ups will be blinded.

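### The primary event/censor split rests on an undefined 'successful completion' label that no stated blinding covers: a bias risk of unknown size, cheap to check

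*Protocol article*

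**What the plan says.** The Outcomes section of the protocol article defines retention as time from randomization to discharge or trial end. Two rules then sort the discharges:

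- Censored: "Patients who are registered as having completed a successful course of treatment will be considered censored at the date of discharge". The only reason given is that the pilot trial did the same.
- Event: "Any reason for discharge, other than completed treatment, will be considered dropout, even if discharge is on patient request".

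On discharge itself the section says "In general, discharge occurs when the patient no longer receive any services". It adds that "practices may vary slightly between sites in terms of their practices when discharging patients" and that "As researchers we are legally and practically unable to influence these decisions". It also says that no site ends OAT against a patient's wishes.

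On blinding, Eligibility criteria says "Participants and clinicians cannot be blinded to the conditions that the participants will be randomized to", but that "the persons who will conduct the assessments at the follow-ups will be blinded". Under Randomization, those follow-ups are telephone interviews. Clinicians and trial interventions says that the clinicians are existing clinic staff and are trained in both conditions.

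Statistical analyses specifies an intention-to-treat Cox regression of retention, with covariates and a random intercept for site.

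**The concern.** The same departure on the same day is either a primary event or a censored time, depending on one registered label. Because OAT is not withdrawn against patients' wishes, many departures should be voluntary. For those, the line between leaving at one's own request (an event) and completing successfully (censored) is a judgement. Continued counselling sets no endpoint that would settle it, since treatment after the initial sessions goes on as needed.

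None of the design's usual protections reaches this label. The blinded interviewers collect self-reported outcomes. Intention-to-treat governs who is analysed in which arm, not how an outcome is classified. The site random intercept absorbs differences in level between sites, not a difference between arms within a site.

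If departures in one arm were more readily called successful, events would leave that arm's count and its retention would look better. The primary HR alone could not separate that from a treatment effect.

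**Working it through.** **Inputs from the article.** N = 137, design HR 0.62, power 80%, alpha 0.05 (Sample size). The censoring and event rules are those under Outcomes.

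**Assumptions, not in the article.** Two-sided test and 1:1 allocation; the shares of discharges labelled successful (s1 in ILC, s0 in MOVE-I), constant over time; the proportion of patients discharged during follow-up.

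**Step 1: the plan's own figure.** Schoenfeld's formula gives (1.960 + 0.842)² / (0.25 × (ln 0.62)²) = 137.4. The stated 137 therefore matches a required number of events, and 137 events give 79.9% power. It matters here only because every censored discharge reduces the event count. How the sample size was set is a separate question.

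**Step 2: HR produced by labelling alone.** Let the hazard of any discharge be the same, h, in both arms. The hazard of a discharge counted as dropout is h(1 − s1) in ILC and h(1 − s0) in MOVE-I, so

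HR = (1 − s1) / (1 − s0).

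| s0 (MOVE-I) | s1 (ILC) | HR |
|---|---|---|
| 10% | 10% | 1.00 |
| 10% | 15% | 0.85/0.90 = 0.94 |
| 10% | 20% | 0.80/0.90 = 0.89 |
| 10% | 30% | 0.70/0.90 = 0.78 |

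With s0 between 5% and 30%, a 5-point gap gives HRs from 0.95 to 0.93. To reach 0.62 by labelling alone, s1 must equal 1 − 0.62(1 − s0): 38% at s0 = 0, 44% at 10%, 50% at 20%, 57% at 30%. That is a gap of about 27 to 38 points. If the shares are reversed between arms, the HR goes above 1 instead.

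**Step 3: type I error.** A log-rank simulation with 137 patients, exponential discharge times, equal true hazards and 8,000 runs per scenario gave these two-sided rejection rates against a nominal 5%:

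| s0 / s1 | 30% discharged | 60% discharged |
|---|---|---|
| 10% / 10% | 4.7% | 4.9% |
| 10% / 20% | 6.1% | 8.0% |
| 10% / 30% | 10.6% | 16.5% |

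The ceiling is reached if all 137 patients are discharged.

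- At 10%/20% there are 137 × 0.85 = 116 events. The shift is 0.118 × √116 / 2 = 0.63, and the error is about 10%.
- At 10%/30% there are 137 × 0.80 = 110 events. The shift is 0.251 × √110 / 2 = 1.32, and the error is about 26%.

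**Step 4: what a check must do.** If every discharge is an event, the label drops out and the HR returns to 1.00 in each scenario. Keeping labelled completers at risk as retained does the opposite. With 60% discharged and 10%/30%, cumulative dropout is 0.54 in MOVE-I and 0.42 in ILC, so the HR is about ln(0.58)/ln(0.46) = 0.70, further from 1 than the primary 0.78.

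**The case against.** The rule is prespecified, identical in both arms and narrow: everything except completion is dropout. The article openly discloses both the lack of blinding and the variation in discharge practice. That variation is between sites, and randomization within site plus the site intercept deals with it. The article does not say who enters the label; that site staff do is an inference from the Outcomes sentences on site practice and from clinicians being clinic employees. Any sensitivity analysis may sit in a statistical analysis plan that is not shown. All of this stands, and the absence of such an analysis is not part of the point.

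A reader might infer that unblinded staff will favour ILC. The documents do not support that: staff are trained in both conditions, and nothing suggests that labels will differ by arm. A reader might also infer that the type I error could be as large as a calculation on 137 events would give. That number of events cannot occur when 10–30% of discharges among 137 patients are censored.

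The objections leave one thing untouched. The article itself ties the endpoint to a label with no stated criterion, set where the arm is known and outside the researchers' control. Disclosure does not show whether the label affected the result.

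**Conclusion.** The point holds as a risk of bias of unknown size and direction, not as a demonstrated bias. The text supports the mechanism: an undefined label decides event or censoring, the stated blinding does not cover it, and the site term cannot remove an arm difference within a site.

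The size rests wholly on assumed labelling shares and discharge proportions. Small differences do little; 10- and 20-point gaps from a 10% base give HRs of 0.89 and 0.78. Labelling alone would need a very large gap to imitate the design effect of 0.62. This is a worthwhile and inexpensive improvement, not a reason to change the primary outcome.

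**What to change.** Keep the primary definition. Prespecify one supporting Cox model, with the same covariates and site term, in which every discharge from the episode is an event whatever the registered reason. Report the number and timing of completion-labelled discharges by arm and site, and interpret the primary HR alongside both.

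The cost is one further run of the same model and one table. The downside is real: the supporting model counts genuine completions as leaving treatment, so it would understate a benefit if ILC truly increases completion. It should therefore be supporting, and not a condition for claiming superiority.

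An analysis that keeps labelled completers at risk as retained should not be offered as a check on labelling. It still uses the label to remove events and, as step 4 of the working shows, enlarges the distortion.

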### Other measures

All patients in Denmark are registered by their personal identification number. The data collected the individual participants in the trial conditions will be compared using data on the same individuals from the Danish Register of Drug Users in Treatment; the Danish National Patient Register; the Danish Registry for Causes of Death; the Psychiatric Central Research Register; and the Danish Central Crime Register. The specific measures include number of offences that led to conviction 12 months post-randomization and number of emergency room contacts 12 months post-randomization. Data on offences and hospitalizations will be collected by uploading the individual data from patients in the trial to a secure server held by Statistics Denmark and linking data with criminal justice data from the Danish Central Crime Register and hospital data from the Danish National Patient Register approximately 24 months after the conclusion of the trial, in order to allow all data to be fully updated.

### Acceptability and feasibility

Acceptability and feasibility will be measured in two ways: first, participants will complete single-item rating scales at follow-up concerning the helpfulness of their counselling sessions [34]. Clinicians will complete similar the Feasibility of Intervention Measure and the Acceptability of Intervention Measure after the completion of their first two sessions, and after the completion of their first two patients [35].

### Case-control

For the case-control study, controls will be identified through the Danish Register of Drug Users in Treatment and will be selected from among people admitted to treatment during the same period as the cases. Controls will be matched to cases on opioid use, criminal history, psychiatric history, age, sex, duration of present treatment, and previous treatment history.

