**Methods:**

The study is a multicenter, randomized, controlled, superiority clinical trial. Participants will be a total of 137 hard-to-treat individuals enrolled in opioid agonist treatment (OAT). Participants will be randomized to either a standard treatment (14 sessions of individual manual-based cognitive behavioral therapy and motivational interviewing (MOVE-I)) or six sessions of ILC followed by nine sessions of MOVE-I. All participants will receive personalized text reminders prior to each session and vouchers for attendance, as well as medication as needed. The primary outcome is retention in treatment. Secondary measures include severity of drug use and days of criminal offending for profit three and nine months post-randomization. A secondary aim is, through a case-control study, to investigate whether participants in the trial differ from patients receiving treatment as usual in municipalities where ILC and MOVE-I have not been implemented in OAT. This will be done by comparing number of offences leading to conviction 12 months post-randomization recorded in the national criminal justice register and number of emergency room contacts 12 months post-randomization recorded in the national hospital register.

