#### Main objectives

To test whether the combination of ILC/MOVE-I will improve treatment retention compared with MOVE-I for patients with externalizing behavior enrolled in OAT.To use case controls from the Register of Drug Abusers in Treatment to examine if ILC and MOVE-I are superior to treatment as usual in municipalities where ILC and MOVE-I have not been implemented in OAT, as measured by number of offences leading to conviction and number of emergency room contacts 12 months post-randomization.

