### Study setting and recruitment

Participants (*N* = 137) will be recruited from OAT in four outpatient municipal treatment centers situated in four Danish cities: Herning, Randers, Aarhus, and Aabenraa. Both current patients and new admissions will be invited to participate. The study is situated at the Centre for Alcohol and Drug Research, Aarhus University.

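### The second main objective asks for superiority over usual treatment from a matched but non-randomised register comparison, which supports only a statement of difference or association, as the abstract words it

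*Protocol article*

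**What the plan says.** Under Main objectives the article lists two items. The first is the randomised comparison of retention. The second uses register controls "to examine if ILC and MOVE-I are superior to treatment as usual in municipalities where ILC and MOVE-I have not been implemented in OAT", measured by convictions and emergency room contacts in the 12 months after randomisation. The Methods part of the abstract describes the same work in other terms: "A secondary aim is, through a case-control study, to investigate whether participants in the trial differ from patients receiving treatment as usual".

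Under Case-control, the controls come from the national register of drug users in treatment and "will be selected from among people admitted to treatment during the same period as the cases". The matching is then given: "Controls will be matched to cases on opioid use, criminal history, psychiatric history, age, sex, duration of present treatment, and previous treatment history".

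Participants enter by a different route. Under Study setting and recruitment, "Both current patients and new admissions will be invited to participate". Under Eligibility criteria they must score three or more on the YouthMap12 externalizing subscale, be able to attend, and consent. They are excluded for a severe mental disorder, for cognitive difficulties, or for "severe aggressive and chaotic behavior that would preclude their participation in the counselling sessions".

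**The concern.** Superiority of a treatment is a causal statement. In this trial randomisation supports such a statement for ILC against MOVE-I, but not for either of them against usual treatment elsewhere. Participants have passed a behavioural screen, agreed to take part and been judged able to attend. Controls have passed none of these filters as far as the article states, and they live in other municipalities. A difference in convictions or emergency contacts could therefore reflect who was recruited, or where, rather than what was delivered.

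At stake is what the trial may conclude. As a main objective of a randomised trial, the result would be read with more authority than its design gives it. The objectives section and the abstract also disagree on both the rank of this comparison and the kind of claim it is to yield, so a reader cannot tell which governs.

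**Working it through.** **1. The two statements of the aim**

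| | Main objectives | Abstract, Methods |
|---|---|---|
| Rank | one of two main objectives | secondary aim |
| Claim | superior | differ |
| Comparison | register controls, other municipalities | the same |

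Both rows on rank and claim conflict.

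**2. Type of design.** The so-called cases are the trial participants. They are chosen because they received the treatments, and convictions and emergency contacts are counted afterwards (Other measures). Selection is by exposure, so this is a matched cohort, not a case-control study.

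**3. What the matching covers**

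| Feature of participants | Counterpart in the matching |
|---|---|
| Externalizing score of three or more | none direct; criminal and psychiatric history are partial proxies |
| Able to attend | none |
| Consented | none |
| No severe mental disorder | psychiatric history, in part |
| No cognitive difficulties; no severe aggressive or chaotic behaviour | none direct |
| Earlier offending | criminal history |
| Earlier emergency contacts | none |
| Time in the current episode | matched |
| Municipality | differs by construction |

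The first row matters on the article's own account: the Background states that externalizing psychopathology correlates with offending after treatment, and convictions are one of the two outcomes here.

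**4. The plan's only effect figure for offences.** Sample size gives a base rate of 0.85, a ratio of 1.43 and 95% power, without group sizes, alpha or number of controls per participant. A Wald test on the log ratio of two Poisson rates has power Φ(|ln 1.43| / SE − z), with SE² = 1/(n0 × 0.85) + 1/(n1 × 0.85 × 1.43). At two-sided 0.05:

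- 68 against 69 (the trial arms): 55%
- 137 against 137 controls: 84%
- 548 controls against 137 participants: 98%

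A value close to 95% needs choices that the article does not state, for example 548 controls with one-sided alpha 0.01 (94.9%). The figure cannot be tied to the register comparison, so 1.43 is no firm benchmark for it.

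**5. Illustration of residual selection.** All inputs are assumed; none comes from the article. The ratio is participants over controls with no treatment effect.

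- *Exclusions.* If a fraction q of controls would have failed them and has r times the conviction rate, the ratio is 1/(1 − q + qr). With q = 0.1, r = 2: 1/1.1 = 0.91. With q = 0.2, r = 3: 1/1.4 = 0.71. This favours the trial treatments.
- *Externalizing score.* If a fraction p of controls would score three or more and such patients have g times the rate of the others, the ratio is g/(pg + 1 − p). With p = 0.7, g = 1.5: 1.5/1.35 = 1.11. With p = 0.3, g = 3: 3/1.6 = 1.88. This goes against the trial treatments.

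These formulas give no credit for the matching. If matching removed half of each on the log scale (the square root), the ranges become 0.95 to 0.85 and 1.05 to 1.37. The two mechanisms pull in opposite directions, and nothing in the article says which is larger.

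**The case against.** The strongest reply is that the article is more careful than the word superior suggests. The objective says that it will examine the question, not that it will prove it. Study objectives names retention as the main aim, Outcomes makes it the only primary outcome, and the register measures stand under Other measures. Criminal history predicts later convictions directly, and psychiatric history bears on the severe-mental-disorder exclusion. All of this stands: the matching narrows the gap, and no result of the randomised comparison depends on this one. It does not close the gap or settle the conflict with the abstract, and the limitations in the Discussion do not mention this comparison.

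Three stronger readings are tempting but not supported.

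- *That controls have no aligned start of follow-up.* The outcome window runs from randomisation, which controls do not have. But time in the current episode is a matching variable, which gives alignment once a reference date is set, and a condensed article may leave that date to the full protocol.
- *That vouchers and reminders confound the comparison.* The Abbreviations define MOVE-I as including both, so they belong to the package under test.
- *That the bias is as large as the effect of interest.* The illustrative ratios rest on assumed inputs, and the ratio of 1.43 is not linked to this comparison.

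**Conclusion.** The concern holds in a limited form. The second main objective is worded as a superiority question, conflicts with the abstract in rank and claim, and rests on a non-randomised comparison. Matching reduces selection in that comparison but does not remove it. A causal superiority conclusion is not supported, whichever way the result falls. A statement that participants differ from matched patients elsewhere, or that the treatments are associated with fewer or more events, can be made.

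The size and net direction of the remaining bias cannot be derived from the documents; the illustration shows only that plausible mechanisms act in both directions. The conclusion assumes that the full protocol adds no control-side version of the eligibility screen.

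**What to change.** 1. Align Main objectives with the abstract: make this a secondary aim and replace superior with differ or associated with.
2. Call the design a matched cohort.
3. Count control outcomes from an index date at which the control is in treatment and has spent the same time in the current episode as the matched participant had at randomisation. Measure all matching variables before that date. Time in episode should not be taken from completed register episodes, because that would condition on later retention, the trial's primary outcome.
4. Adjust the 12-month counts for the same person's convictions and emergency contacts in the 12 months before the index date. This partly overlaps with matching on criminal history for convictions, but is new for emergency contacts.
5. State the unmeasured externalizing score and the confounding with municipality as limitations.

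The cost is rewording and some register programming. The pre-index counts come from the crime and patient registers that are already to be linked. The downside is a more modest claim.

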Compared with patients with other substance use disorders, people with opioid use disorders have the highest risk of criminal activity, psychiatric comorbidity, poly-substance use, infections, such as HIV and hepatitis C [10, 11], as well as excess mortality [12, 13] and a high degree of somatic comorbidity [14]. However, this is primarily due to the fact that opioid use disorders represent the most severe end of the substance use disorder spectrum, and while opioid use disorder is associated with antisocial personality traits, this is mostly as part of its overall relationship with a general propensity for substance use disorders [15]. Once opioid use disorder is established, however, criminal offending may be reduced by the provision of medication assisted treatment [16].

The dual burden of using a drug with particularly heavy consequences and externalizing behavior problems may put some patients at very high risk for a range of adverse outcomes. A considerable barrier to benefitting from treatment is staying in contact with the system for a sufficient time; around 30% of patients drop out of psychosocial treatment across types of substances and treatment, and dropout rates are even higher for more disadvantaged patients and treatments that demand time and concentration [17, 18]. Furthermore, a growing body of evidence suggests that patients with externalizing and criminal behavior are particularly hard to retain in treatment and offer relevant help but that improved retention and treatment effects may be associated with substantially lower costs of crime [19, 20]. Thus, improving retention and outcomes for people with externalizing disorders who enroll in OAT is of crucial importance.

One way to improve retention and outcomes is the use of contingency management (CM) in the form of voucher-based reinforcement therapy [21]. However, the evidence base for specially tailored programs to serve the needs of people with opioid use disorder who are high on externalizing problems is extremely limited. A recent narrative review based on a small handful of studies indicated that cognitive behavioral therapy and CM, or milieu therapy alone or in combination with other interventions, have not been differentially effective for patients with opioid use disorder and antisocial personality disorder [22].

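### The register comparison matches controls on criminal history but not on earlier emergency-room contacts, so a difference in emergency-room use that predates the trial could be read as a treatment effect

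*Protocol article*

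**What the plan says.** The Main objectives section of the protocol article sets as its second aim, using controls from the treatment register, "to examine if ILC and MOVE-I are superior to treatment as usual in municipalities where ILC and MOVE-I have not been implemented in OAT". Two register counts over the year after randomization serve as its outcomes: convicted offences and emergency-room contacts. The abstract describes the same aim more softly, as asking whether participants differ from such patients.

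The Case-control section defines the controls in two sentences. The first says that they are "selected from among people admitted to treatment during the same period as the cases". The second fixes the variables used for matching: "Controls will be matched to cases on opioid use, criminal history, psychiatric history, age, sex, duration of present treatment, and previous treatment history".

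The Other measures section names both register outcomes and says that participants will be linked to criminal justice data and to "hospital data from the Danish National Patient Register" about 24 months after the trial concludes.

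The Statistical analyses section adjusts secondary outcomes for their baseline values and describes how a count model for convictions will be chosen. It gives no model for emergency-room contacts.

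**The concern.** The comparison with register controls is not randomized. Matching is the only clearly stated protection against groups that differed from the outset. The list covers earlier offending for the offence outcome, but has no equivalent for the emergency-room outcome. Psychiatric history is matched; other hospital history is not.

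If some people use emergency rooms persistently more than others, and participants and controls differ in this before the index date, the 12-month comparison will reproduce that difference. Because the objective is worded as superiority, the difference would then be credited to, or held against, ILC and MOVE-I.

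Equal starting rates cannot be taken for granted. Participants are selected on an externalizing score of three or above, on consent and on ability to attend, and none of these is matched. They could move emergency-room use in either direction.

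**Working it through.** **Step 1: outcomes against matching variables.**

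| Outcome of the second objective | Its own history in the matching list? | Baseline adjustment stated elsewhere? |
|---|---|---|
| Offences leading to conviction | Yes, criminal history | Count model given; whether baseline adjustment extends to it is unclear |
| Emergency-room contacts | No | No model given; baseline adjustment is attached to secondary outcomes, and contacts are not in that list |

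**Step 2: inputs for an illustration.** The article gives no figure of its own to reproduce here. It gives 137 participants. It gives no emergency-room rate, number of controls, between-person variance or baseline gap, so these are assumptions: 137 controls, mean 1 contact per year, between-person (gamma) variance k = 1, the same personal rate before and after the index date, and no treatment effect.

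**Step 3: unadjusted comparison, participants' usual rate 25% higher.** The variance of a group's log mean count is (1/mean + k)/n.

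- SE = √[(1/1.25 + 1)/137 + (1/1 + 1)/137] = √(3.8/137) = 0.167
- ln 1.25 = 0.223, and 0.223/0.167 = 1.34
- Chance of p<0.05 = P(Z > 1.96 − 1.34), about 27%

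Two simulations of this setting gave ratios of 1.25 and 1.26 with rejection in about 25% and 29% of studies. Over means of 0.5 to 2 and k of 0.5 to 2 the formula gives 16–47%. For a rate 50% higher, the simulations gave a ratio of about 1.5 and rejection in about 69–72%.

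A second parameterization uses SE = √{φ[1/(137·b·r) + 1/(137·b)]}, with base rate b of 0.5 to 1.5 and overdispersion φ of 1 to 3. The chance of p<0.05 is 5% at r = 1, 12–66% at r = 1.25 and 11–57% at r = 0.8. A false finding can thus arise in either direction.

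**Step 4: adjusting for the prior-year count.** At mean 1 and k = 1 a yearly count has variance 1 + 1 = 2, and two years' counts have covariance 1, so the slope of one year on the other is 1/2. Adjustment then removes about half the gap: 0.25 − 0.5 × 0.25 = 0.125. The simulations agree, with an adjusted ratio of 1.11 and rejection in 11–12%. Comparing before-to-after change gave 1.00 and about 6%, but the 1.00 follows from assuming a constant personal rate.

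**Step 5: precision.** With no imbalance, adjustment lowers the SE from 0.170 to about 0.148. (0.170/0.148)² = 1.32, equivalent to about 32% more patients.

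**The case against.** **The analysis may already deal with it.** A matching list does not rule out covariate adjustment, the article is condensed, and the analysis plan is not shown. The Statistical analyses section may also use the word secondary broadly, since the models that follow cover sessions attended and convictions, neither of which is in the secondary outcome list. It stands that adjustment is not excluded, and the missing emergency-room model is not in itself the fault. But the matching list is stated as definite, and it treats the two outcomes of one objective differently.

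**The figures are assumed.** This stands in full. Nothing in the document supports a gap of 25% or 50% remaining after matching on seven variables. Nor does it say that prior-year hospital records will be extracted; that they can be is an assumption about a register already being linked.

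**A stronger reading: controls outside OAT.** Controls are drawn from people admitted to treatment and matched on opioid use, while the Background says that "criminal offending may be reduced by the provision of medication assisted treatment". A reader might infer that controls not receiving OAT would be used and that the effect of OAT would be credited to ILC and MOVE-I. The document does not support this. The abstract and Main objectives both place the comparator in OAT in non-implementing municipalities, and duration of present treatment naturally refers to OAT. What remains is that the Case-control section does not carry the restriction over. No size should be attached to this.

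**A second extension: the randomized arms.** A reader might ask for the same covariates when ILC is compared with MOVE-I. Randomization protects that comparison from systematic baseline differences, and choosing a covariate for precision is ordinary analysis-plan content. It lies outside the control definition.

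**Conclusion.** The point holds, limited to the register comparison. The stated matching leaves the history of one of its two outcomes uncontrolled, and no passage clearly makes good the gap. The randomized primary outcome is unaffected.

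The possible bias has unknown size and direction. The illustration shows only that a modest existing difference could produce a nominally significant result with no treatment effect, and that the prior-year count would remove about half of it. These figures depend wholly on the assumed rate, variance, number of controls and imbalance.

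The OAT restriction is a matter of aligning wording. Controlling for earlier emergency-room contacts will not by itself justify the word superior: externalizing score, consent and ability to attend remain unmatched, so residual confounding persists.

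**What to change.** In the Case-control section:

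1. Add the number of emergency-room contacts in the 12 months before the index date to the matching variables, or enter that count as a covariate in the emergency-room model. Enter the prior-year number of offences in the conviction model in the same way.
2. Report the before-to-after change ratio, participants against controls, as a sensitivity analysis, because one prior year's count removes the difference only in part.
3. Carry over the comparator implied in the abstract and Main objectives: limit controls to people in OAT at the index date, in municipalities where neither programme has been implemented.
4. Word the objective and its result as an association.

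The cost is a few sentences, one earlier year of data from registers already being linked, and a slightly smaller pool of matchable controls. As linkage is planned about 24 months after the trial concludes, the change can be fixed before these data are seen.
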